## Discussion

The present study represents an attempt to improve control of the illness, the quality of life of the patients at our center, and their adherence to the treatment for asthma, using telemedicine as the main tool, in combination with normal care. There is scientific evidence that carrying out more continuous follow-up of patients increases their knowledge of the pathology and of how to monitor it, improves communication between patient and professional, and personalizes resources in accordance with the needs of the individual, thereby empowering the patient to achieve greater control of his or her asthma [1, 10, 11]. It has also been demonstrated that keeping the main comorbidities (allergies, obesity, rhinitis, nasal polyposis, GERD, and stress) under control is essential to improving the health of the patient with asthma [1, 4].

There is at present a varied typology of interventions based on telemedicine to achieve improved management of the illness. The most frequently used, in terms of channel of communication, are online chats and meetings [26, 27], mobile applications [28–32], SMS [33, 34], and websites [34–36]. In terms of content, they are remote monitoring by means of questionnaires and collecting of spirometric data [28–34], remote consulting with the health center by means of the tool [26–29, 33], and distance learning [26, 27, 30, 32, 33, 35, 36]. Of note, there are studies that focus on a single sphere of content, while others include more than one. The study that we are presenting here includes several of these interventions.

In several studies telemedicine was used as a tool for controlling asthma and improving the quality of life of the users [26–36]. However, it is difficult to establish standards for the content of an application for asthma given the diversity of the interventions and the variability of the results obtained from them [37].

In the studies that we analyzed it was demonstrated that interventions that used a mobile application to provide information to participants regarding inhaled therapy and a personalized plan of action improved control of the illness and adherence to treatment [29, 32]. In contrast, in those studies not making using of a mobile application, but rather a website or SMS, the improvements were not significant, nor were there clinical benefits [34–36]. Another point to make note of is that applications that include reminders sent by SMS, both for taking medication and for completing questionnaires, showed a much higher level of compliance than did the interventions that did not include reminders [26, 34]. Nemanic T et al. achieved a participant compliance level of 80% with ACT and 96% with PEF thanks to SMS reminders [34].

In terms of communication between the patient and the professionals, the applications that allowed the patient to maintain direct contact with the healthcare professionals achieved improved asthma self-management [27, 29]. They also produced a reduction in daytime symptoms, number of hospitalizations, and visits to the emergency room.

Our intervention has sought to draw together elements from all the interventions that have achieved significant results and assemble them in a personalized application with which the patient will have available all the information needed to improve control over the illness, and through which the healthcare team can intervene in a much more efficient manner.

### Ethical considerations

The study is in compliance with the principles of the Helsinki Declaration, and it was approved by the Ethical Committee of the Bellvitge University Hospital (reference ICPS023/22). The personal data obtained will be confidential (Organic Law 3/2018, December 5, governing protection of personal data and the guarantee of digital rights) which supersedes Organic Law 15/1999, December 5, on the protection of personal data, and by extension, in the UE (General Regulation (UE) 2016/679 on the protection of data). Total confidentiality of the data obtained is guaranteed by the assignment of an identification number to each patient and by the creation of a database specific to this study in which data will be included in an encoded format.

All of the tests carried out by the patients in the present protocol are part of normal clinical practice in the treatment of patients with asthma. Therefore, participation in the study does not represent any additional risk to that associated with the normal care provided to asthmatic patients.

The data collected for this study will be encoded and only the principal investigator of the study and his collaborators will be able to associate the data with the medical history of the patients. Therefore, the identity of the patients will not be revealed to anyone except in the event of a medical emergency or legal requirement thereof.

Access to the personal information shall remain limited to the principal investigator of the study and his collaborators, as well as to the clinical research ethical committee when required to verify data and study procedures, at all times respecting the confidentiality of the data in accordance with the applicable legislation.

### Limitations

As this is a single-center study, the results may not be representative of the general population, which limits our ability to extrapolate the findings to different clinical settings. In an attempt to offset this limitation, and to ensure that the results are as extrapolable as possible, we will use the standards laid out in the Spanish Guide for the Management of Asthma (GEMA) [1]. To learn the degree of control of the illness we will take into account the number of exacerbations suffered in the past year, the asthma symptoms measured with ACT [19], and pulmonary function, using as measuring tools the PEF and the FEV1. With the aim of determining the degree of adherence to treatment we will use the TAI questionnaire and will review the electronic history of withdrawal from prescribed medication [1, 20]. For quality of life, we will make recourse to the AQLQ and the HAD [21, 22].

Given that the proposed intervention has simple masking, the research team and the clinical staff will be aware at all times which patients belong to which group, and this could influence the behavior of the staff as well as the manner in which the results are evaluated. As a result of randomization, it may be difficult to ensure that the groups are completely comparable in all areas.

Another limitation to bear in mind is the time stipulated for follow-up, which is limited and which may impede assessment of the effectiveness of the telemedicine program over the long-term in the control of asthma.

Finally, the participants may not comply completely with the recommendations made to them, or they may abandon the study prematurely, which would cause skewing in the results and render assessment of the real effectiveness of the telemedicine program in the control of asthma difficult. In addition, assessment of the control of asthma often involves subjective measurement of symptoms and quality of life, which could be influenced by the individual perception of the participants.

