### Calculation of the sample

In order to calculate the sample size, a screening of 60 patients seen in the pneumology unit of the center was made with the ACT questionnaire, in order to learn the degree of current control of the asthma of those patients.

With a CI of 95% and a standard deviation of 4.95, the average ACT score of the patients seen in our center was 18.43 ± 1.25. The calculation of the sample size was based upon the established aims. We used the Granmo 7.12 program for two independent averages, accepting an alpha risk of 0.05 and a beta risk of 0.2 in bilateral contrast. Some 54 subjects were determined to be needed for each group in order to detect a difference equal to or greater than 3 units in the ACT questionnaire [16, 17]. We assumed a common standard deviation of 4.95 (obtained by screening in our center) and calculated a rate of loss in follow-up of 20%.

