### Analysis of the data

The continuous variables are expressed as mean and standard deviation in case of normal distribution, and median and interquartile range in case of non-normal distribution. The qualitative variables are to be defined as frequencies and percentages. For comparison of the continuous variables the variance analysis method (ANOVA) or the Kruskal-Wallis test will be used. For analysis of the main assessment, the Chi-squared test will be used. Stepwise logistic regression models will be used to select the subgroup with parameters significantly associated with poor control of asthma. A priori, the factors to be included in the analysis are age, number of years suffering asthma, education level, IMC, smoking, environmental exposures, pre-BD FEV1, post-BD FEV1, FeNO, blood eosinophils, general and specific blood IgE, ACT, TAI, HAD, AQLQ, number of exacerbations, and control of comorbidities that affect asthma (GERD, rhinitis, nasal polyposis, overweight/obesity, and smoking). Statistical significance will be set at *p* < 0.05.

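### The tests named for ACT make no use of baseline or 6-month scores for patients missing a later visit, although the article allows for 20% loss and concedes that dropout would skew the results

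*Protocol article*

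**What the plan says.** Calculation of the sample sets the test parameters, "accepting an alpha risk of 0.05 and a beta risk of 0.2 in bilateral contrast", and the target, to "detect a difference equal to or greater than 3 units in the ACT questionnaire". On spread it says "We assumed a common standard deviation of 4.95". It "calculated a rate of loss in follow-up of 20" percent and concludes that "Some 54 subjects were determined to be needed for each group".

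Variables names ACT as the main variable. It is assessed in both groups at the start, at 6 months and at 12 months (V1, V2 and V3 in Table 2), and the results are to be compared. No single primary time point is named. Table 2 adds monthly ACT through the app for the intervention group only.

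Analysis of the data assigns the chi-squared test to the main assessment. For the rest it says: "For comparison of the continuous variables the variance analysis method (ANOVA) or the Kruskal-Wallis test will be used". It names no longitudinal method for ACT.

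Limitations says participants may not follow the recommendations fully, or "they may abandon the study prematurely, which would cause skewing in the results". No offsetting measure follows, whereas the single-centre limitation in the same section does get one (use of the national guideline's standards).

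**The concern.** The article identifies a bias, collects data that could reduce it, and names tests that do not use those data. Each named test compares groups on one value per patient. Run on observed 12-month scores, it uses only patients with a 12-month score, and what is known about the others at V1 and V2 goes unused.

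The inflation for loss protects power. It does nothing about bias, which arises if the patients who leave differ in asthma control and do so differently by arm. That is plausible here because contact differs: the intervention arm has monthly questionnaires, automatic alerts and messaging, while controls have three visits, a telephone number and a peak-flow diary. The direction cannot be foreseen. Losing poorly controlled app patients would flatter the app, and losing poorly controlled control patients would hide part of its effect.

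**Working it through.** **The plan's own figure.** Inputs from Calculation of the sample: difference 3, SD 4.95, two-sided alpha 0.05, power 0.80, loss 20%.

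- Evaluable per group: 2 × (1.960 + 0.842)² × 4.95² / 3² = 42.7, so 43.
- Inflated for loss: 43 / 0.8 = 53.75, so 54. The stated figure reproduces.
- Standard error with 43 completers per arm: 4.95 × √(2/43) = 1.07.
- Power: Φ(3/1.07 − 1.96) = 80.2%. The allowance covers the loss of precision.

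**Bias among completers.** The article gives no between-visit correlation, dropout mechanism or timing of loss, so these are assumptions:

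- ACT at V1, V2 and V3 is trivariate normal with SD 4.95 and equal correlation between visits, varied from 0.4 to 0.7.
- Means are 18.43 throughout in the control arm (the screening mean: "the average ACT score of the patients seen in our center was 18.43 ± 1.25"), and 18.43, 21.43 and 21.43 in the intervention arm. The true 12-month difference is 3.
- Loss is 20% in each arm. Where it depends on ACT, the log-odds change by 1 per SD of the driving score.
- There are 300,000 simulated patients per arm, so sampling noise is small.

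Two estimates were compared: the completers-only difference in mean 12-month ACT, and one that fills missing values by regression on V1 and V2 within arm (V1 alone where V2 is missing). The second is what a likelihood-based model or multiple imputation targets.

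With low-ACT patients more likely to leave the intervention arm, and random loss in the control arm:

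| Loss follows | V2 available for those lost | Bias, completers only | Bias, using V1 and V2 | Share removed |
|---|---|---|---|---|
| 6-month score | all | +0.35 to +0.58 | about 0 | about all |
| 6-month score | half | +0.38 to +0.62 | +0.10 to +0.12 | 68–84% |
| 6-month score | none | +0.34 to +0.59 | +0.18 to +0.23 | 38–69% |
| unseen 12-month score | all, half or none | +0.83 to +0.89 | +0.37 to +0.77 | 13–55% |

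Ranges run over the correlations. The sign reverses if the selective loss is in the control arm.

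**Equal dependence in both arms.** Bias is within 0.05 of zero for either estimate, under either mechanism.

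**Opposite patterns.** At correlation 0.6, with loss following V2, V2 always observed, and poorly controlled patients leaving the control arm:

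- random loss in the app arm: completers-only estimate about 2.5;
- well-controlled patients leaving the app arm, slope 0.5: about 2.2;
- the same, slope 1: about 2.0.

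Using V1 and V2 returns about 3.0 in all three.

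**Effect on power.** With 43 completers per arm, an estimate centred on 2.5 has power Φ(2.5/1.07 − 1.96) of about 65%. One centred on 2.0 has about 47%.

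**The case against.** The strongest objection is that this is a missing-data gap, and a journal article commonly leaves missing-data handling to the full protocol or analysis plan. The Analysis of the data section is one paragraph and states no analysis set. This stands as far as silence goes: the absence of a missing-data rule is not the point made here. The point concerns the methods that are named, for an outcome measured three times.

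A reader might go further and infer the following, which the documents do not support:

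- *That the plan drops every patient without a 12-month ACT.* No completers-only rule is stated. Chi-squared or ANOVA could be run on imputed data, and chi-squared could count losses as not controlled.
- *That 12 months is the primary time point.* Three assessments are listed and none is singled out.
- *That the investigators expect skewed results.* The 20% is a sample-size allowance, and Limitations presents abandonment as a possibility.
- *That the 6-month scores would largely correct the bias.* Full recovery needs loss to depend on ACT that was observed. Patients lost before V2 have no 6-month visit score, and the monthly scores exist in one arm only.
- *That stopping the app counts as withdrawal.* Table 1 lists only voluntary withdrawal from the study, loss to follow-up and death.

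Three further objections stand in part. Differential loss by arm is conjecture, and without it there is little bias in the mean difference. A bias of 0.5 units is about half the standard error of 1.07. The sizes are for a difference in means, the scale of the sample-size calculation, and not for the chi-squared test assigned to the main assessment, whose response categories the article does not define.

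**Conclusion.** The point holds in limited form. The article allows for 20% loss and concedes that dropout would skew results. Yet the tests it names for ACT, applied to observed scores at a visit, ignore V1 and V2 for patients who lack the later visit.

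The possible bias in a completers-only 12-month mean difference is about 0.35 to 0.6 units when loss in one arm follows the 6-month score, and about 0.85 when it follows the unseen 12-month score. It reaches about 0.8 to 1.0 in the opposite-pattern cases at correlation 0.6. It is negligible when loss depends on ACT equally in both arms.

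These figures rest on assumed correlations, mechanisms and timing and on a normal model for ACT. They show what could happen, not what will. Using V1 and V2 reduced the bias in every one-arm scenario examined, but the share removed ran from nearly all to 13%. The change is worth making because the data are already being collected. The sample size is not in question.

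**What to change.** In Analysis of the data, state that ACT is analysed for all randomised patients in their assigned arm by one of two methods:

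- a likelihood-based repeated-measures model on V1, V2 and V3 with an arm-by-visit term; or
- multiple imputation from V1 ACT, V2 ACT and arm.

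Take the 12-month contrast as the main reading if the sponsor confirms that time point. Add one delta-shift sensitivity analysis, in which the values filled in for patients lost are shifted by a range of amounts, because loss that depends on unseen scores is not fully corrected by either method. Say in the text that the analysis reduces dropout bias and removes it only if loss depends on observed ACT.

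The cost is a few sentences and slightly more analysis work. No new data, visits or patients are needed.

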## Data Availability

No datasets were generated or analysed during the current study.
